### Data analysis

3.6

Participant characteristics (age, sex, ethnicity) will be described using measures of frequency distribution. All other outcomes (FAS score, CFQ‐11 total and subscale scores, MFIS total and subscale scores, COMPASS‐31 score, HADS score, B‐IPQ score, BIS score, change in walking speed, HRV during quiet sitting in each session, HRV throughout each task (physical, cognitive), VAS score at six time points in each session, NRS at four time points during each task, RPE at four time points during each task, somatosensory attenuation pre‐ and post‐task in each session, somatosensory gating pre‐ and post‐task in each session) will be described using measures of central tendency and distribution. A list of all outcomes is provided in Table 1.

### Statistical analysis

3.7

A series of statistical analyses will be conducted to compare the descriptive characteristics of the two groups (long COVID/neither long COVID nor fatigue). The characteristics to be compared are age, gender, trait fatigue (FAS score, CFQ‐11 total score, CFQ‐11 physical subscale score, CFQ‐11 mental subscale score), impact of trait fatigue (MFIS physical subscale score, MFIS cognitive subscale score, MFIS psychosocial subscale score), mood (HADS‐A score, HADS‐D score), illness beliefs (BIPQ score), and autonomic symptoms (COMPASS‐31 score). Gender will be analysed as a categorical variable. A chi‐square test will be used to compare the gender distribution between the groups. All other variables will be analysed as ratio data and compared across groups using an independent samples if the data meet parametric assumptions (normality, verifying equal variance) and a Mann–Whitney *U* test if the data do not meet parametric assumptions.

Results will be summarized using a measure of central tendency (mean or median) and spread (standard deviation or interquartile range), test statistics, and *P*‐values for ratio data and frequency, percentage, chi‐square values, and *P*‐values for categorical variables.
Hypothesis 1Pre‐task (baseline) somatosensory attenuation will be different between individuals with long COVID fatigue and controls. We will also attempt to replicate the Baker et al. (2023) finding that somatosensory gating is not different between individuals with long COVID fatigue and controls. The independent variable will be ‘participants’, which consists of two categories: ‘individuals with long COVID fatigue’ and ‘controls’. The two dependent variables will be ‘somatosensory attenuation’ and ‘somatosensory gating’, measured at baseline during the first session participants attend.

This will be tested using a multivariate analysis of variance to test for an overall difference in somatosensory processing between populations, and to explore the differences in somatosensory gating and attenuation. We will check that the following assumptions are met: multivariate normality, independence and equal variance. If we find the multivariate analysis of variance is significant, we will conduct follow‐up univariate analysis of variance for somatosensory attenuation and somatosensory gating to identify specific contributions to the effect and will apply Bonferroni correction to control for the increased risk of Type I error.
Hypothesis 2: State fatigue following exertion will be predicted by somatosensory attenuation at baseline, somatosensory gating at baseline, the presence of long COVID (long covid/controls), and the type of task (cognitive/physical). Performance fatigability will be considered a moderator variable in these relations. State fatigue prior to exertion will be included as a covariate in this analysis.

This will be tested using a linear mixed model:

$$Y_{ijk}=\mu +a_{i}+b_{j}+c_{k}+d_{ik}+e_{ik}+f_{ik}+g_{ijk}+\left(f_{ik}\times a_{i}\right)+\left(f_{ik}\times b_{j}\right)+\varepsilon_{ijk}$$
where:

*Y_ijk_
*: state fatigue following exertion in the *i*‐th group (long COVID/control) during task *j* (cognitive/physical) for the *k*‐th subject.μ: the overall mean of state fatigue following exertion.
*a_i_
*: the effect of the *i*‐th group (fixed effect: long COVID vs. control).
*b_j_
*: the effect of the *j*‐th task (fixed effect: cognitive vs. physical).
*d_ik_
*: the baseline somatosensory attenuation for the *k*‐th subject in the *i*‐th group.
*e_ik_
*: the baseline somatosensory gating for the *k*‐th subject in the *i‐*th group.
*f_ijk_
*: the performance fatigability for the *k*‐th subject in the *i*‐th group during the *j*‐th task.
*g_ijk_
*: the state fatigue prior to exertion for the *k*‐th subject in the *i*‐th group during the *j*‐th task (covariate).(*f_ik_
*×*a_i_
*): the interaction term between performance fatigability and group.(*f_ik_
*×*b_j_
*): the interaction term between performance fatigability and task.
*ϵ_ijk_
*: the residual error term, assumed to be normally distributed.
Hypothesis 3: The change in somatosensory attenuation (Research Question 3a) and somatosensory gating (Research Question 3b) from pre‐ to post‐task will be predicted by the change in state fatigue from pre to post, fatigability, the presence of long COVID (long COVID/controls), and the type of task (cognitive/physical).

We will use linear mixed models to test these hypotheses, with separate models for somatosensory attenuation and somatosensory gating:

$$Y_{ijk}=a_{i}+b_{j}+c_{ijk}+d_{ijk}+u_{0i}+\varepsilon_{ijk}$$
where:

*Y_ijk_
*: attenuation or gating at baseline in the *i*‐th group (long COVID/control) during task j (cognitive/physical) for the k‐th subject.
*a_i_
*: the fixed effect of the *i*‐th group (long COVID vs. control) on baseline attenuation.
*b_j_
*: the fixed effect of the *j*‐th task (cognitive vs. physical) on baseline attenuation.
*c_ijk_
*: the change in state fatigue from pre to post in the *i*‐th group, during task *j*, for the k‐th subject, affecting baseline attenuation.
*d_ijk_
*: the change in fatigability in the *i*‐th group, during task *j*, for the *k*‐th subject,
*u*
_0_
*
_i_
*: random intercept for group *i*, capturing group‐level variability
*ϵ_ijk_
*: residual error term, representing random variability and measurement error not explained by the fixed effects.
Hypothesis 4: Among individuals with long COVID, trait fatigue will be effected by mood, illness beliefs, autonomic symptoms, increase in state fatigue induced by a physical task, the increase in state fatigue induced by a cognitive task, and autonomic nervous system function.

This will be tested using a linear mixed effects model:

$$Y_{i}=\mu +a_{i}+b_{i}+c_{i}+d_{i}+e_{i}+f_{i}+u_{0i}+\varepsilon_{i}$$
where:

*Y_i_
*: trait fatigue for individual *i*.μ: the overall mean of state fatigue following exertion.
*a_i_
*: mood for individual *i*.
*b_i_
*: illness beliefs for individual *i*.
*c_i_
*: autonomic symptoms for individual *i*.
*d_i_
*: change in state fatigue induced by physical task for individual *i*.
*e_i_
*: change in state fatigue induced by cognitive task for individual *i*.
*f_i_
*: autonomic nervous system function for individual *i*

*u*
_0_
*
_i_
*: random intercept capturing individual‐specific variability in trait fatigue not explained by the fixed effects.
*ϵ_i_
*: residual error term representing random variability and measurement error.

We will check the following assumptions of the regression models: linearity, independence, homoscedasticity, normality and multicollinearity.

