There are two similar, but distinct, phenomena involved in somatosensory processing (Kilteni & Ehrsson, 2022). Attenuation is the suppression of somatosensory input that arises from one's own movement (reafferent input) in comparison to somatosensory input that arises from external sources (exafferent input). Gating is the suppression of externally generated somatosensory input during voluntary movement in comparison to when at rest. Somatosensory gating has been reported not to differ between individuals without long COVID and those reporting long COVID fatigue that had a moderate‐to‐severe impact on daily living (Baker et al., 2023). Previous studies in clinical conditions that experience fatigue have focused on somatosensory attenuation (Parthasharathy et al., 2022; Wolpe et al., 2018), but this has not been studied in long COVID. In this study we aim to replicate the Baker et al. (2023) finding that somatosensory gating is not different in individuals with and without long COVID fatigue, and extend this by asking whether somatosensory attenuation is different between individuals with and without long COVID fatigue (Research Question 1).

Fatigue can be considered as both a stable and enduring characteristic, reflecting how a person feels over weeks or months, and an instantaneous experience, reflecting how a person feels at a given moment. These concepts are referred to as trait and state fatigue, respectively. Although somatosensory processing has been studied in relation to trait fatigue (Baker et al., 2023; de Doncker et al., 2021), it is not well studied in relation to state fatigue. Definitions and measures of fatigue in long COVID cover different dimensions, such as physical, cognitive, emotional, psychosocial, and general fatigue and post exertional malaise ([name] et al., 2024 [Unpublished raw data]). It is unclear if different dimensions share the same underlying mechanisms. Here we focus on state fatigue in two of these dimensions—physical and cognitive. We will quantify relations between somatosensory processing and state fatigue induced by both a cognitive and a physical task (Research Question 2) and quantify how these are related to trait fatigue (Research Question 4). This will add to our understanding of the relations between and mechanisms underlying different dimensions of state fatigue and trait fatigue in long COVID.

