### Sample size

3.8

The study is powered to address Research Question 1a. Previous research indicates an effect size of 0.78 for differences in somatosensory attenuation between young and older individuals (Parthasharathy et al., 2022). Powering the current study to detect an effect size of 0.78 between two independent means for Research Question 1a—somatosensory attenuation in individuals with and without long COVID—with an α error probability of 0.05 and a power of 95% and based on a non‐directional two‐tailed hypothesis requires 44 participants per group (G*power 3.1.9.7). Dropout is not expected to impact Research Question 1a or 1b, as it involves initial measurements during the first session. However, there is a potential for dropout to impact the subsequent research questions, which rely on participants returning for a second session.

The sample size gives us power of 90% to detect an effect of 0.70 between two groups at two repeated time points with alpha error probability of 0.05 for Research Questions 2 and 3, or a power of 80% to detect an effect of 0.60. A dropout rate of 10% would mean that our power to detect these effect sizes decreases to 60%. The approach for addressing Research Questions 2 and 3 ensures that the study is adequately powered to detect correlations of 0.50 and 0.40, respectively. The code used to calculate the outcome measure is available at https://github.com/smancuso/R‐ Code/blob/cc90c623c4dc733fe5c93ef5a795dde010152c63/Power.R

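### Hypothesis 1 seeks to replicate an absence of difference in gating, but plans only a gated difference test and sets no criterion for replication

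*Protocol article*

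**What the plan says.** The Introduction (section 1) gives one aim as replicating an earlier "finding that somatosensory gating is not different in individuals with and without long COVID fatigue". Section 3.7 repeats it under Hypothesis 1 as an attempt to replicate the "finding that somatosensory gating is not different between individuals with long COVID fatigue and controls". Attenuation, by contrast, is predicted to differ.

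Both outcomes share one analysis: "This will be tested using a multivariate analysis of variance to test for an overall difference in somatosensory processing between populations". The univariate step is conditional: "If we find the multivariate analysis of variance is significant, we will conduct" separate ANOVAs for attenuation and gating, and the investigators "will apply Bonferroni correction to control for the increased risk of Type I error".

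Section 3.8 states that "The study is powered to address Research Question 1a", that is, attenuation. It uses an "effect size of 0.78 between two independent means" and arrives at 44 per group. It gives no power or precision for gating (Research Question 1b). The exploratory analyses in section 3.7.1 rerun Hypothesis 1 with age, time of day and session order added. They include no equivalence margin, interval criterion or Bayes factor for gating.

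**The concern.** A test for a difference can reject equality but cannot establish it. If the result for gating is non-significant, the data may fit no difference, a moderate difference, or both. Two features of the plan make this worse for gating:

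- The Bonferroni step lowers the significance level for gating. That protects a claim of difference, but it makes a null result easier to obtain.
- The univariate comparison is conditional on the MANOVA. If the MANOVA is not significant, no gating-specific test is planned, although gating has its own research question.

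At stake is whether Research Question 1b can be answered in the form in which the Introduction and Hypothesis 1 pose it. The attenuation comparison and its sample size are not affected.

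**Working it through.** **Inputs from the protocol.** 44 per group, two-sided α 0.05, power 95%, d = 0.78 for attenuation (section 3.8); MANOVA, then Bonferroni-corrected ANOVAs if it is significant (section 3.7).

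**Assumptions.** MANOVA at 0.05; Bonferroni over two outcomes, so 0.05/2 = 0.025; normal data with equal variances; true gating differences of 0.3 to 0.6 SD (the protocol gives no effect size for gating); true attenuation difference of 0 or 0.78 SD; correlation between the two measures of 0 in the tables, with -0.5, 0.3 and 0.5 also tried.

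**1. The protocol's own figure.** Power for two independent means is the probability that |T| exceeds the critical value, where T is noncentral t with 2n - 2 degrees of freedom and noncentrality d√(n/2). At n = 44 the noncentrality is 0.78 × √22 = 3.66. Power is 94.7% at 43 per group and 95.1% at 44. The stated 44 per group reproduces.

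**2. One gating test on its own, n = 44 per group.** Probability that a true difference is not declared, by the same formula:

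| True gating difference (SD) | α 0.05 | α 0.025 |
|---|---|---|
| 0.3 | 71% | 80% |
| 0.4 | 54% | 65% |
| 0.5 | 36% | 47% |
| 0.6 | 21% | 30% |

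**3. The planned sequence.** Simulated with 400,000 runs per scenario, correlation 0. The undeclared runs are split by cause.

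| True gating difference (SD) | Attenuation difference (SD) | MANOVA not significant, gating not tested | Gating tested, not significant | Total undeclared |
|---|---|---|---|---|
| 0.3 | 0.78 | 5.9% | 74.5% | 80% |
| 0.4 | 0.78 | 4.0% | 61.3% | 65% |
| 0.5 | 0.78 | 2.4% | 44.8% | 47% |
| 0.6 | 0.78 | 1.3% | 28.5% | 30% |
| 0.3 | 0 | 78.3% | 4.8% | 83% |
| 0.4 | 0 | 64.0% | 5.0% | 69% |
| 0.5 | 0 | 47.2% | 4.4% | 52% |
| 0.6 | 0 | 30.5% | 3.3% | 34% |

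The other correlations change the totals by less than 3 percentage points. They shift the split between the two causes, but the larger cause stays the same in each half of the table.

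**4. Precision for gating.** The standard error of the difference is √(2/44) = 0.213 SD. The expected half-width is 1.663 × 0.213 = 0.35 SD for a 90% interval and 0.42 SD for a 95% interval.

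**5. What an equivalence analysis could show.** Two one-sided tests (TOST) at 0.05 each amount to requiring the 90% interval to lie within ±m. With a true difference of zero, power is approximately 2Φ((m - 0.354)/0.213) - 1. For m = 0.5 this is 2Φ(0.68) - 1, about 50%. Simulated powers are 17% at ±0.4, 50% at ±0.5, 75% at ±0.6, 89% at ±0.7 and 95% at ±0.78 SD. The number per group for 80% power, 2((1.645 + 1.282)/m)², is 69 at ±0.5 and 48 at ±0.6.

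**The case against.** The strongest reply is that the protocol never says a non-significant result will be reported as a successful replication. It promises only an attempt, and section 2 words Research Question 1b neutrally, asking whether gating differs; a difference test does address that. This stands. A reader might infer that the study will claim replication through lack of power, but that predicts how results will be interpreted, and the documents do not support it. What they do show is a null aim with no rule for deciding whether it was met.

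Second, in the scenario without an attenuation difference, most undeclared runs are failures at the MANOVA step: 78 of 83 points at 0.3 SD and 47 of 52 at 0.5 SD. In those runs the plan yields no gating-specific conclusion, so they should not be read as null findings on gating. This also stands, and is why the table separates the causes.

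Third, the gating procedure copies the earlier study to allow comparison (section 3.4.7), and section 3.6 commits to descriptive summaries of gating. Estimates will therefore exist. Descriptive summaries, however, do not define what counts as agreement with a null finding.

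Fourth, the study is powered for attenuation, and interpretive detail may be left to a fuller plan. The first part limits the weight of the point. The second does not remove it, because the article itself states both the null aim and the difference test meant to address it.

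**Conclusion.** The point holds as a mismatch between a stated aim and its stated analysis. The planned inference can detect a gating difference but cannot support a conclusion that there is none, and no criterion for replication is given. A real difference of 0.5 SD would go undeclared about half the time (47 to 52%), and one of 0.3 SD about four times in five (80 to 83%). These rates depend on assumed gating effects and on the α levels listed in the working. They hardly depend on the correlation between the two measures.

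The point does not extend to saying that the investigators will present non-significance as replication. It does not touch the sample size for attenuation, which reproduces. It should be corrected, but it does not threaten the comparison for which the study is powered.

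**What to change.** - Estimate the group difference in gating whatever the MANOVA result, and report it with its confidence interval (expected 90% half-width about 0.35 SD).
- State that a non-significant difference alone is inconclusive.
- Claim replication only if the 90% interval lies within an equivalence margin that the sponsor justifies on gating grounds before the data are seen.
- Do not borrow 0.60 from section 3.8. It is a detectable effect for Research Questions 2 and 3, not a gating difference judged negligible. At ±0.60 SD, equivalence would still be declared about 40% of the time with a true difference of 0.3 SD, 24% at 0.4 SD and 12% at 0.5 SD.
- State what 44 per group can deliver at a true difference of zero: TOST power of about 50% at ±0.5, 75% at ±0.6 and 89% at ±0.7 SD.

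The cost is a few sentences of analysis text plus the work of justifying a margin, for which the protocol offers no basis at present. No extra participants or measurements are needed. The downside is that the gating result may have to be reported as inconclusive: at a true difference of zero this would happen about half the time with ±0.5 SD and a quarter of the time with ±0.6 SD.

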The sensation of fatigue may be independent from objective measures of performance (Bailey et al., 2007; Krupp & Elkins, 2000; Lou et al., 2003). For example, Fietsam et al. (2023) found that individuals with long COVID reported more fatigue than individuals without long COVID but had similar levels of performance decline on an isokinetic fatigue task. The decline in an objective measure of performance over a discrete period of time is termed performance fatigability (Enoka et al., 2021). Understanding the association between fatigue and fatigability has been identified as an important goal for clinical research (Kluger et al., 2013). We will address this in our second research question by quantifying whether the change in performance over the cognitive and physical tasks (performance fatigability) is related to state fatigue induced by that task, whether this moderates the relation between somatosensory processing and state fatigue, and whether this is impacted by long COVID (Research Question 2).

In addition to understanding if somatosensory processing predicts fatigue, it is also of relevance to ask if fatigue impacts somatosensory processing (bidirectional arrows in Figure 1, blue boxes). This would potentially indicate that activities that increase fatigue and cause performance fatigability, could lead to disrupted somatosensory processing, further increasing the fatigue and fatigability. This will be addressed in our third research question, where we ask if the change in somatosensory attenuation (Research Question 3i) and somatosensory gating (Research Question 3ii) from pre‐ to post‐task is predicted by the change in state fatigue from pre to post task, fatigability during the task, population (long COVID/controls) and task (cognitive/physical).

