## RESEARCH QUESTIONS

2

Research Question 1: Are pre‐task (baseline) somatosensory attenuation (Research Question 1a) and somatosensory gating (Research Question 1b) different between individuals with long COVID fatigue compared to controls?

Research Question 2: Is state fatigue following exertion predicted by somatosensory attenuation at baseline, somatosensory gating at baseline, the presence of long COVID (long COVID/controls), and the type of task (cognitive/physical), and is performance fatigability a moderator variable in this relation? State fatigue prior to exertion will be included as a covariate in this analysis.

Research Question 3: Is the change in somatosensory attenuation (Research Question 3a) and somatosensory gating (Research Question 3b) from pre‐ to post‐task predicted by the change in state fatigue during exertion, fatigability, the presence of long COVID (long COVID/controls), and the type of task (cognitive/physical)?

Research Question 4: Among individuals with long COVID, is trait fatigue predicted by the increase in state fatigue induced by a physical task, the increase in state fatigue induced by a cognitive task, mood, illness beliefs, autonomic symptoms and autonomic nervous system function?

This study will provide the first comprehensive investigation into the role of somatosensory processing in long COVID fatigue and explore how prominent symptoms in long COVID (autonomic dysfunction, altered mood, beliefs about the meaning of symptoms) interact with somatosensory processing, fatigability and the experience of fatigue.

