#### Physical task

3.3.2

The physical task is the 6‐minute walk task (6MWT). This requires participants to walk at their fastest pace for 6 min, aiming to cover as much ground as possible. Participants are able to take breaks at any point, with the clock continuously running (American Thoracic Society, 2002).

The test will be carried out on a self‐paced treadmill (Motek Medical). Four retroreflective markers will be placed on the pelvis over the left and right anterior and posterior superior iliac spines. The position of these markers will be recorded by a three‐dimensional optoelectronic motion capture system (Vicon Nexus, Oxford, UK) and streamed in real time into D‐flow software version 3.36.2 (Motek Medical). D‐flow software will monitor the position of these markers and control treadmill speed according to the position of the participant. This allows the participant to walk on the treadmill at a fluctuating speed, including slowing to a stop for rests whenever they want. The speed of the treadmill belt and the distance covered will be recorded within D‐flow software. Participants will be fitted with a security harness and will be allowed to familiarize themselves with the self‐paced treadmill for up to 5 min prior to the start of the physical task. Participants will be allowed to hold onto the siderails for stability.

The 6MWT induced fatigue in individuals with multiple sclerosis (McLoughlin et al., 2016), indicating it is an appropriate task to induce fatigue in long COVID participants. It is not anticipated that this task will cause significant fatigue in healthy (control) participants. However, healthy (control) participants will be asked to perform the task to provide control data and inform interpretation of data from participants with long COVID fatigue.

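### The Hypothesis 2 model has no term for fatigability moderating the attenuation and gating relations with state fatigue, although the protocol states that moderation

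*Protocol article*

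**What the plan says.** The protocol article states the moderation question in three places.

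- Introduction: the second research question will examine "whether this moderates the relation between somatosensory processing and state fatigue, and whether this is impacted by long COVID". The relation said to be moderated is the one between somatosensory processing and state fatigue.
- Research Questions (2): Research Question 2 lists baseline attenuation, baseline gating, long COVID status and type of task as predictors, then asks "is performance fatigability a moderator variable in this relation".
- Statistical analysis (3.7), Hypothesis 2: the same four predictors are listed, followed by "Performance fatigability will be considered a moderator variable in these relations".

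The linear mixed model for Hypothesis 2 contains group (a), task (b), a subject-indexed term (c), attenuation (d), gating (e), fatigability (f), state fatigue before exertion (g), f×a and f×b. The definitions under the equation describe the two products as "the interaction term between performance fatigability and group" and "the interaction term between performance fatigability and task". Attenuation is defined as "the baseline somatosensory attenuation for the" k-th subject, and gating likewise. Neither appears in a product.

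**The concern.** In a linear model, fatigability moderates the effect of attenuation if the attenuation slope changes with fatigability. That is the f×d coefficient, and for gating it is f×e. Without these terms the plan cannot estimate or test the part of the moderation question that concerns sensory processing.

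The Timeline (3.9) plans a Stage 2 registered report, so the printed equation is the prespecified model. If the two interactions are added after data collection, they are a departure from it. If they are not added, a stated question goes unanswered, and a reader of the report could take a result for f×group or f×task as an answer to the sensory question.

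**Working it through.** **Inputs.** The three statements of the question, the Hypothesis 2 equation with its term definitions, and the Planned exploratory analysis (3.7.1). The point depends on no stated figure. The sample size of 44 per group gives 44 + 44 = 88 participants and 88 × 2 = 176 participant-sessions. That figure reproduces: for an effect size of 0.78 and two-sided alpha of 0.05, noncentral-t power is 0.947 at 43 per group and 0.951 at 44.

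**Step 1: stated relations against model terms.**

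| Relation with state fatigue | Stated as moderated by fatigability | Interaction in the equation |
|---|---|---|
| Attenuation (d) | Introduction, Research Question 2, Hypothesis 2 | none |
| Gating (e) | Introduction, Research Question 2, Hypothesis 2 | none |
| Group (a) | Research Question 2, Hypothesis 2 | f×a |
| Task (b) | Research Question 2, Hypothesis 2 | f×b |

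The equation and the definitions agree, so the gap is not a fault of text extraction.

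**Step 2: what the printed model implies.** Write β for the coefficients. In the printed model the slope of state fatigue on attenuation is β_d, whatever the value of f. With f×d added it becomes β_d + β_fd × f, and moderation is the statement that β_fd is not 0. The same holds for gating with β_e and β_fe.

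**Step 3: is it supplied elsewhere?** The Planned exploratory analysis adds age, time of day and session order, a mediation analysis of autonomic dysfunction, correlations and test–retest reliability. None introduces a product of fatigability with attenuation or gating.

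**Step 4: could f×group or f×task stand in?** An illustrative simulation used assumed values: 88 participants, two tasks, independent standardised predictors, participant and residual standard deviations of 0.7, a true f×d coefficient of 0.3, and 200 runs. The subject-indexed term c, which the article does not define, was taken as a participant random intercept.

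- Printed model: f×group was significant at 5% in 8% of runs and f×task in 6.5%, with mean coefficients of 0.007 and −0.008. The Monte Carlo standard error at 5% is √(0.05 × 0.95 / 200) = 0.015, so both rates lie within two standard errors of nominal.
- With f×d and f×e added: f×d was significant in 98% of runs, with mean estimate 0.29.
- With a true f×d of 0: f×d was significant in 6.5% of runs.

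Under these assumptions the printed interactions do not pick up the sensory moderation, and the added term does. This shows identifiability only. It does not estimate the power of this study.

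**Step 5: scale of fatigability.** In the cognitive task it is based on the balanced integration score, a standardised quantity (3.4.5). In the walk it is a change in speed in m/s (3.4.6). A single f×d or f×e coefficient across tasks would mix these units, and centring alone does not remove that.

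**The case against.** The strongest reply is that the model does test moderation. Under the wider wording of Research Question 2 and Hypothesis 2, group and task are among the moderated relations, and f×a and f×b are their proper parameters. This stands. A reader might infer that no part of the moderation question can be answered, or that the two printed interactions are mislabelled. The documents support neither reading: only the attenuation and gating parts lack a parameter.

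It can also be said that the matter is secondary. The abstract names the baseline comparison of somatosensory processing as the primary objective and describes the fatigability associations as exploratory, and the study is powered for Research Question 1a. The main effects of attenuation and gating on state fatigue are still estimated. This stands too, so it would be too strong to say that the study's sensory account of fatigue goes untested.

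A reader might go further and call the absence of a group×task term an error, because of the walk the article says "It is not anticipated that this task will cause significant fatigue in healthy (control) participants", while the modified cognitive task raised fatigue by 59 − 26 = 33 mm in a pilot. The documents do not support this. Neither Research Question 2 nor Hypothesis 2 asks for a group×task effect. The pilot was in 15 young healthy volunteers, not the study's controls aged 18 to 69, and an expectation of no significant fatigue is not a rise of 0 mm. The printed model also contains f, g, f×a and f×b, so the fitted task difference can differ between groups wherever fatigability or prior fatigue does.

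Finally, the Introduction's closing phrase about the impact of long COVID is ambiguous. If it means that the moderation itself differs by group, three-way terms would be needed. The wording does not settle this, so they are not claimed here as missing.

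**Conclusion.** The plan is wrong as written on a limited point. Of four relations said to be moderated by fatigability, two (group, task) have an interaction parameter and two (attenuation, gating) have none. The missing two are the relations the Introduction names. Followed as printed, the plan leaves that part of Research Question 2 untested, however large the true effect.

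The conclusion rests on the text and the equation. It does not depend on the simulation's assumed values or on how the undefined subject term is read. It does not extend to the primary comparison, to the sensory main effects, or to moderation by group and task.

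**What to change.** Add f×d and f×e to the Hypothesis 2 model. Standardise fatigability within task, and centre attenuation and gating. Name these two terms as the tests of whether fatigability moderates the somatosensory relations, and keep f×a and f×b for group and task. Even after standardising, a pooled coefficient assumes that one standard deviation of fatigability moderates equally in both tasks; the plan should say so.

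If the authors do not intend to test sensory moderation, the alternative is to restrict the moderation wording in the Introduction, Research Question 2 and Hypothesis 2 to group and task.

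The first option raises the fixed effects from 9 to 11, counting the intercept and taking c as random, with slightly wider intervals. The information is less than 176 participant-sessions suggest: attenuation and gating are indexed by subject, so each has at most 88 distinct values. The Sample size section (3.8) gives no power for these interactions specifically, so their estimates should be reported with intervals and a null result read with caution. No extra data are needed.
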